### Ethics Approval

The study received ethical approval from the Deakin University Human Research Ethics Committee (2021-258).

## Results

The iMove app and integration with SORD were finalized in August 2022. Recruitment was initiated in October 2022. So far, 6 participants (2 female and 4 male) have provided their consent and enrolled in the study. They have completed baseline measurements and started using iMove. The mean age of 6 participants is 56.8 years, and they were diagnosed with T2D for 9.4 years on average.

## Discussion

### Overview

We present an MRT to evaluate the development of a Sit Less and Move More JITAI intervention in people with T2D [20]. The proximal and distal main effects of the sedentary and PA interventions on reducing sitting time and increasing standing or walking time (ie, nonsitting time), along with their univariate effects, will be evaluated. Moreover, the most effective behavior change technique will be recognized. Furthermore, the most critical contexts (eg, location: home or workplace) in which users are most responsive to interventions will be identified.

Too much sitting is a distinct behavior consideration from too little exercise for increasing the risk of cardiovascular disease [20]. Practical and integrated approaches involving both Sit Less and Move More have been introduced for risk reduction [20]. It is expected that interventions delivering a combination of Sit Less and Move More would add to the overall daily activity of an individual rather than focusing on at least 150 minutes of weekly exercise [20].

To our knowledge, there are no previous MRT studies targeting SB and PA among people with T2D. Other studies have focused on the general public including healthy sedentary adults [14] and university students [29]. The study by Klasnja et al [14] showed that the 6-week MRT intervention (antisedentary or walking vs no suggestion) among healthy sedentary adults (n=44) was effective to increase the average 30-minute step counts (ie, within 30 minutes after the intervention) by 14%. The study by Figueroa et al [29] conducted a 6-week MRT with university students (n=99) to improve their PA level. They showed that receiving the intervention (motivational messages and feedback on step counts vs no suggestion) increased daily steps by 729 steps, but this effect was diminished over time to –33 steps a day. They recommend that future studies need to take into account both user context and preferences [29].

These theory-based MRT studies were mainly focused on walking [14] rather than standing. Incorporating standing into the intervention package could make the Sit Less and Move More concept more practical. Replacing sitting time with standing could be considered a medium in which the most sedentary populations (eg, T2D) may make the initial transition from an inactive lifestyle to a more active lifestyle [30].

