## Methods

### Design

A 6-week MRT will be conducted (see Figure 1). Using this design, participants will be randomly assigned an intervention option (Sit Less message, Move More message, or no intervention) at each relevant decision point.

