#### Sample Size

A total of 22 participants are estimated to detect a small proximal treatment effect size of 0.13 for increasing nonsitting time with 80% power at the level of 5% statistical significance. This was based on the assumptions of 5 decision points per day, a constant randomization probability of 0.7, and an expected participant availability of 70% [16].

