### Eligibility Criteria

Eligible participants will be adults with T2D, aged between 35 and 65 years, who own an Android smartphone (version 7.0 or higher) and currently interact or engage with apps, have no limitations (including physical problems and medical complications) to engage in low- and moderate-intensity PA, are able to communicate in English, and can provide informed consent.

Volunteers who use other activity trackers and mobile apps that target PA, highly active people, those diagnosed with T2D less than 3 months ago, and people with psychiatric problems, attention, or memory issues will be excluded. We assume highly active people as those who meet World Health Organization (WHO) recommendation of 10,000 steps per day or 150 minutes of moderate to vigorous PA per week. The International Physical Activity Questionnaire—Short Form will be used to assess activity levels [17]. A 1-week run-in period will assess nonadherence with the activity tracker. Individuals with more than 50% incomplete data will be excluded.

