### Intervention

#### Overview

Through the iMove app, participants will receive a series of Sit Less and Move More intervention messages (notifications) to serve as cues to action [21] and increase readiness to engage in activity. A pop-up message will appear on the phone screen with a sound effect when a notification is received. There will be 2 intervention options, which include Sit Less (sedentary interruption and transition to standing) and Move More (walking) for 1.5-3 minutes, approximately equivalent to 500-1000 steps, and a control option (no messages). Participants can switch off the push notification for a certain amount of time on any given day.

A list of messages is provided in Multimedia Appendix 1.

Notifications are adapted to 4 different context dimensions, including time of day, day of the week (weekend vs weekdays), location (home vs workplace), and weather conditions (good or suitable for PA, rainy and cold or not suitable for PA). Notifications are delivered on 5 occasions (decision points) throughout the day and include morning, lunchtime, afternoon 1, afternoon 2, and evening (details are presented in the “Decision Points” section below).

At each decision point, participants are randomized only if they are available (ie, they are not driving, not sleeping, not active already, and are connected to the internet). The following probabilities are used for randomization: 70% in the intervention (35% SB, 35% PA) and 30% as active control at each particular decision point. GPS will assist with the recognition of driving if the user is on the move. A preset time (9 PM to 8 AM) will be considered for rest and sleeping. In addition, both driving and sleeping can be manually modified by users.

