### Distal Outcome

The distal outcomes of interest are the “average weekly time spent sanding and walking altogether, that is, nonsitting time” and the “average time spent being in the sitting state.” Moreover, we will also assess total sitting, standing, walking, and exercising time.

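### The article promises distal main effects of Sit Less and Move More, but one within-person randomisation policy for everyone leaves weekly averages with no usable comparator

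*Protocol article*

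**What the plan says.** - **Claim (Discussion, Overview).** "The proximal and distal main effects of the sedentary and PA interventions on reducing sitting time" and on increasing standing or walking time are to be evaluated.
- **Distal outcomes (Methods, Distal Outcome).** These are the "average weekly time spent sanding and walking altogether, that is, nonsitting time" and the average time spent sitting. Both are summaries over weeks or over the study, not over an hour.
- **Randomisation (Methods, Design).** "participants will be randomly assigned an intervention option (Sit Less message, Move More message, or no intervention) at each relevant decision point".
- **Probabilities (Methods, Intervention, Overview).** "70% in the intervention (35% SB, 35% PA) and 30% as active control at each particular decision point". The Sample Size section treats the 0.7 as constant.
- **Sizing (Methods, Sample Size).** The target of 22 people rests on this requirement: "detect a small proximal treatment effect size of 0.13 for increasing nonsitting time with 80% power at the level of 5% statistical significance".
- **Aims and Primary Analysis.** The primary aim and the behaviour-change-technique aim are both framed proximally. The primary contrast is message against no message over the following hour.
- **Run-in (Eligibility Criteria).** "A 1-week run-in period will assess nonadherence with the activity tracker". The article gives this week no role as a baseline for the distal outcomes and does not say whether messages are switched off during it.

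**The concern.** A main effect of an intervention on a weekly average needs weeks, or people, with and without that intervention. The control here is an occasion without a message inside a person's day, not a group of people. All participants follow one policy for the whole study, and each receives both message types interleaved. A rise in weekly nonsitting time therefore has nothing to be set against. It also cannot be divided between Sit Less and Move More.

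Over the same weeks participants wear the sensor, see their activity on the app's home tab and set goals in it (Intervention Platform). An uncontrolled trend would mix all of this with season and with any effect of the messages. What is at stake is how the distal results may be described. Under the present sentence, a change over time could carry the label of an intervention effect.

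**Working it through.** **1. The plan's own figure.** Inputs: 42 days × 5 points = 210 decision points, availability τ = 0.7, message probability ρ = 0.7, standardised proximal effect 0.13, 5% significance, 80% power. The usual microrandomised-trial F test has p and N − q − p degrees of freedom (p effect terms, q nuisance terms) and noncentrality

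λ = N · d′[τρ(1 − ρ) Σ Z_t Z_t′]d.

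For a constant effect and N = 22, λ = 22 × 0.7 × 0.7 × 0.3 × 210 × 0.13² = 22 × 30.87 × 0.0169 = 11.5.

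| Effect and test | N for 80% power | Power at N = 22 |
|---|---|---|
| Constant effect, 1 df | 18 | 0.893–0.896 |
| Constant effect, intercept + linear day (2 df) | 22–23 | 0.797–0.805 |
| Constant effect, intercept + linear + quadratic day (3 df) | 26 | 0.710–0.723 |
| Linear effect starting at 0, 2 df | 18 | 0.906–0.911 |
| Quadratic effect starting at 0, peak day varied, 3 df | 21–24 | 0.773–0.831 |

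(Ranges are over q = 1 to 3 and, in the last row, peak day.) The article does not state the shape of the effect, so the shape is my assumption. Under the 2-df constant and the quadratic forms, 22 is reproduced. The figure is thus consistent with a calculation for the proximal effect, and no distal quantity enters it.

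**2. What each outcome can be compared with.**

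- *Next-hour sitting, standing, walking:* at each available point the same person is randomised to Sit Less, Move More or nothing. This is a randomised contrast.
- *Weekly or study-average times, whole intervention:* nobody is assigned to go without messages. There is no randomised contrast.
- *Weekly or study-average times, each component:* nobody is assigned to one type only. At 147 available points (step 3) the expected count is 147 × 0.35 = 51.5 of each type per person. There is no randomised contrast.

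The Introduction draws the same line. It describes microrandomised trials as explaining causal links between components and proximal effects, and assigns overall intervention effects to conventional randomised trials.

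**3. Could chance differences in dose between people stand in for a comparator?** Assume every participant has 210 × 0.7 = 147 available points.

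- Mean messages per person: 147 × 0.7 = 102.9.
- SD: √(147 × 0.7 × 0.3) = √30.87 = 5.56, a CV of 5.4%. The 95% range is 102.9 ± 1.96 × 5.56, about 92 to 114.
- Probability that a given participant receives none: 0.3^147 ≈ 1.4 × 10⁻⁷⁷.
- Standard error of a between-person slope on dose with N = 22, averaged over 20,000 simulated dose sets: 0.0407 outcome SDs per message.
- Extrapolated from no messages to the mean dose: 0.0407 × 102.9 ≈ 4.19 SDs.
- Effect detectable with 80% power: 2.8 × 4.19 ≈ 11.7 SDs.

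For scale, two parallel groups of 11 would detect 2.80 × √(2/11) = 1.19 SDs.

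**The case against.** **The operative plan is proximal.** The claim is one sentence in the Discussion. No distal model or test is specified, and the Introduction presents distal outcomes as an accumulation of proximal effects. The sentence may mean no more than following weekly totals. This stands as a limit on weight. It does not remove the point: the sentence names main effects of the two interventions, and the Distal Outcome section of Methods makes the weekly averages part of the trial. The fault is a stated property that the design lacks, not a detail left to an analysis plan.

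**Randomisation is not confined to one hour.** A reader might infer that distal effects cannot be estimated in any sense, or that only the next hour is identified. That goes too far. Effects of a single message over a longer window are identified under the same policy. Week-to-week dose also varies by chance. With 35 × 0.7 = 24.5 available points a week, messages average 17.15 with SD √(24.5 × 0.21) = 2.27. Pooling 22 × 6 = 132 person-weeks is far more precise than step 3. With person effects (110 df), 2.8 × 17.15 / (2.27 × √110) is about 2.0 within-person weekly SDs, if weekly errors are independent.

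That still does not provide a usable comparator:

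- A message-free week lies 17.15/2.27 = 7.6 SDs below the mean, so the answer rests on assumed linearity far outside the data.
- It assumes no carry-over between weeks, which sits badly with effects meant to accumulate.
- Availability requires not already being active, so earlier messages can change later availability. Conditioning on the available points in a day or a week may therefore condition on a consequence of treatment.

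The article plans none of these analyses.

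**Regression to the mean.** Because highly active people are excluded, a reader might infer that a drift towards more activity is to be expected. The documents do not show this. Exclusion uses a questionnaire, whereas the outcomes come from the thigh sensor.

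**Misreporting.** A reader might infer that a weekly rise will be published as causal. The article does not say so, and its remark about informing policy makers concerns the findings as a whole.

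**Conclusion.** The point holds, with moderate weight. As described, the design gives no usable comparator for the effect of the whole intervention, or of either component, on weekly or average sitting and nonsitting time. The sentence promising distal main effects therefore claims more than the trial can deliver. This conclusion rests only on one policy applying to all participants throughout, which the article states.

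The defect is one of identification, so its size is essentially qualitative. The 11.7 SD figure is an illustration for study-long averages. It assumes equal availability of 70%, a linear dose response and independent participants. A confidence interval for an uncontrolled change would not measure the problem.

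The proximal aims, the sample size and the primary analysis are not called into question by this point.

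**What to change.** 1. In the Discussion overview, restrict main effects of Sit Less and Move More to the proximal outcomes.
2. In the Distal Outcome section, state that these outcomes will be reported as descriptive, uncontrolled within-person weekly trends with 95% CIs, with no causal attribution to the intervention or to either message type.
3. Use the run-in week as the baseline only if it is confirmed to be message-free. Otherwise describe the trend across the six study weeks alone.

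The cost is a change of wording and a weaker claim on distal outcomes. Randomisation, sample size, data collection and the primary analysis stay as they are.

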### Limitations and Strengths

Due to the data-intensive nature of this study and the reliance on mobile apps for data transfer, heavy data loads may complicate data transfer to the backend server and generate missing instances. Even though multiple troubleshooting steps have been taken to develop iMove, such issues could still occur on certain smartphones with restricted manufacturers’ system mandates. A key strength of this study is the incorporation of standing as a measured outcome. Because the focus of this MRT is on supporting people with T2D transition from sedentary to more overall physical activities, assessing transitional states, that is, standing, seems relevant. Assessing standing time, distinct from sitting and moving time, is expected to provide more robust evidence on how such Sit Less and Move More MRT performs.

### Conclusions

Overall, the results of this study will inform the optimization of digital behavior change interventions to reduce SB and increase PA among people with T2D. Moreover, the findings will provide practical implications to clinicians concerned about recommending high-intensity exercise to older people with T2D. Finally, policy makers will be informed about simple smartphone-based interventions to reduce the burden of sedentariness among people with chronic diseases (eg, diabetes).

## Appendix

Multimedia Appendix 1 An example list of iMove notification.

## Abbreviations

API: application programming interface
JITAI: just-in-time adaptive intervention
mHealth: mobile health
MRT: microrandomized trial
PA: physical activity
SB: sedentary behavior
SORD: Sedentary Behavior Detector
T2D: type 2 diabetes
WHO: World Health Organization
